### Selection of Centers and Subjects

Centers were selected after a site selection screening taking into account the number of recanalization therapies per year, median process times and the readiness to participate with dedication in the intervention. Randomization into an instant and a delayed intervention cohort would be desirable. However, due to the limited number of stroke centers (*n* = 7) and their heterogeneity, this approach is not feasible. Therefore, all seven centers will undergo the intervention and observation phases simultaneously and a comparison will be made between the pre-test-post-test results of all seven centers grouped together.

All patients over the age of 18 years who are admitted directly to the participating centers and receive IVT (primary endpoint: door-to-needle time) in the context of an acute stroke are eligible irrespective of whether they receive additional EVT or not. If EVT is performed, then the EVT-specific processing time will also be acquired (secondary endpoints). Written informed consent will be obtained from all patients or their legal representatives before the transfer of data to the sponsor. Patients who had been secondarily transferred to the stroke centers for EVT (“drip-and-ship”) and patients suffering in-hospital stroke will be excluded from the trial.

Observation phase 1: All direct-to-center stroke patients receiving thrombolysis and/or thrombectomy in the 3 months before the intervention phase.

Observation phase 2: All direct-to-center stroke patients receiving thrombolysis and/or thrombectomy in the 3 months after the intervention phase.

A pilot trial on the efficacy of a fixed stroke team algorithm and regular simulation-based stroke team training in our regional stroke network consisting of 7 stroke units showed a shortening of the network-wide median “door-to-needle” time by 12 min (43, IQR 30–60 to 31, IQR 24–42 min). A priori sample size calculation based on this data yielded a minimal number of 110 patients in each group to prove the comparative efficacy of the composite intervention on the primary endpoint with a statistical power of 0.8 and a type 1 error probability of <0.05. The seven tertiary care stroke centers perform 80–250 thrombolyses per year and should jointly be able to recruit 200 patients in each intervention phase considering the potential dropout rate for missing reports or informed consent in 1/3 of the patients. The centers will be explicitly motivated to record all consecutive patients and they will be obliged to prove that adequate efforts have been made via a monitored screening log.

We will present the median and 25–75 percent interquartile ranges (IQR) of the process times and test differences between the intervention phases for statistical significance via the Wilcoxon-Mann-Whitney Test. The answers provided within the questionnaire capturing satisfaction with the interdisciplinary teamwork, safety climate, stress recognition and error handling, as well as staff satisfaction and identification with the workplace, will be recorded using an ordinal 5-point Likert scale.

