Structured team training based on crew resource management (CRM) has been successfully implemented into emergency medicine, intensive care and surgery. In these contexts, training has led to a significant fall in the mortality rate (up to 18%) (20, 21). To our knowledge, there have been only a few reports on the effect of simulation training on process times in acute stroke care. Existing studies rely on one-time interventions at a simulation facility (22), trained hospitals with little prior experience (23) and/or used retrospective case analyses as a comparator (23, 24). We have previously applied the stroke team approach to the sponsor's stroke admissions team (16) and consequently to our regional stroke network (17), which at the time consisted of seven stroke units. In that study, we found that the intervention (algorithm design, introducing CRM, and simulation training) was effective in reducing the network wide door-to-needle time from a median of 43 min (IQR 30–60 min) to 31 min (IQR 24–42 min) (16) and door-to-groin-time from 59 min (IQR 35–102 min) to 43 min (IQR 28–81 min) (25). However, these studies were limited to a regional network consisting of heterogeneous stroke units of different sizes with and without the capacity for EVT. The multicentric study in the stroke network relied on data entry by the local investigators without central source data verification. By testing the stroke team concept in seven high volume academic tertiary care stroke centers with the 24/7 capacity for thrombectomy in a multicentric pre-test-post-test study, we aim to control some of these limitations and measure the effectiveness of the intervention more reliably. A cluster randomization by center would have been desirable, but the heterogeneity in between centers (e.g., hospital infrastructure, rural vs. urban catchment area, case load, and percentage of drip-and-ship patients) does not permit this. Therefore, we opted for a prospective pre-test-post-test design with central source data monitoring.

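### One unstratified rank test across seven heterogeneous centres does not guarantee the stated 5% type I error if centre mix or centre performance changes between phases

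*Protocol article*

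**What the plan says.** In the protocol article, Data Analysis makes median door-to-needle time the primary endpoint. The plan is to present medians with interquartile ranges and to "test differences between the intervention phases for statistical significance via the Wilcoxon-Mann-Whitney Test". Selection of Centers and Subjects states that "a comparison will be made between the pre-test-post-test results of all seven centers grouped together". Neither section mentions a stratum, a centre effect or clustering.

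The design is repeated measurement of the same centres: "all seven centers will undergo the intervention and observation phases simultaneously", in two 3-month windows separated by 6 months. The Discussion gives as its reason for not randomising by centre "heterogeneity in between centers (e.g., hospital infrastructure, rural vs. urban catchment area, case load, and percentage of drip-and-ship patients". Data Analysis gives annual thrombolysis volumes of 80 to 250 per centre, expects 200 patients per phase, and allows for one third being lost to missing reports or consent. It also requires a monitored screening log.

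Both the test and the pooling are stated. This is a fixed choice, not a detail left to an analysis plan that is not shown.

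**The concern.** The pooled test treats some 400 patients as independent draws from one distribution per phase. The intervention acts on centres, and there are seven. Two things can then be mistaken for an intervention effect:

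- **Centre-by-phase drift.** Staffing or rotas change within a centre over the 6-month gap. Every patient in that centre moves together, but the test counts this as independent patient variation.
- **A shift in centre mix.** If the loss to consent or missing reports differs by centre and by phase, slow and fast centres carry different weights before and after. The pooled median then moves although no centre has changed.

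This affects the only primary test. The Discussion itself expects improvement to be hard to show, because the targeted centres already have medians of 30 min or below. When small gains are expected, a spurious shift of around a minute matters.

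**Working it through.** **1. The plan's own figure.** The article gives no quantity for centre variation. Its one computed figure is the sample size, which "yielded a minimal number of 110 patients in each group" from the pilot values ("43, IQR 30–60 to 31, IQR 24–42 min") "with a statistical power of 0.8 and a type 1 error probability of <0.05". With SD = IQR width/1.349, the two phases have SDs of 30/1.349 = 22.2 and 18/1.349 = 13.3, pooled 18.3. Two-sided, n = 2(1.96 + 0.84)² SD²/12² gives 37 per group for SD 18.3 and 54 for SD 22.2. Dividing by the lowest rank-test efficiency, 0.864, raises the latter to 63. So 110 is not reproduced; it may rest on inputs that are not shown. The planned 200 per phase exceeds all of these, so sample size does not decide this point.

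**2. Stable centres.** Simulation with no true effect, 200 patients per phase, seven centres with volumes of 80–250, lognormal times, two-sided 5%, 3,000–4,000 runs per setting. With stable centre effects and the same expected mix, the pooled test rejects in 4.5–4.9% of runs at intraclass correlations of 0.05–0.30. With exactly fixed centre numbers it is conservative, falling from 4.4% to 2.0%.

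**3. Centre-by-phase drift.** Assumptions: within-centre log SD 0.44, between-centre log SD 0.20, volumes evenly spaced from 80 to 250. The squared patient shares then sum to Σw² = 213,050/1,155² = 0.160.
- Variance that the test allows for: 2(0.44² + 0.20²)/200 = 0.002336.
- Extra variance when each centre's pre-to-post change has SD τ: τ² × 0.160.
- Inflation of the standard error: r = √(1 + 0.160τ²/0.002336). Type I error ≈ 2[1 − Φ(1.96/r)].

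| SD of a centre's change | at 30 min | r | formula | simulated rank test |
|---|---|---|---|---|
| 5% | 1.5 min | 1.08 | 7.0% | 6–7% |
| 7.5% | 2.25 min | 1.18 | 9.6% | 9% |
| 10% | 3 min | 1.30 | 13.1% | 13% |

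Here τ is the SD of the change. If each phase instead fluctuates independently with SD 5%, 7.5% or 10%, the change has an SD √2 times larger (7.1%, 10.6%, 14.1%) and simulated type I error is 8%, 14% and 20%.

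**4. Shift in centre mix.** Assumptions: no centre changes, phase 1 shares are 1/7 each, and the two slowest centres report half as many patients in phase 2. Phase 2 shares are then 1/6 for five centres and 1/12 for two. The total is kept at 200 per phase.
- θ = Σᵢ Σⱼ w₁ᵢ w₂ⱼ Φ((mᵢ − mⱼ)/(σ√2)), with m the log centre medians, evenly spaced in minutes.
- SE = √(401/(12 × 200 × 200)) = 0.0289, and z = (θ − 0.5)/SE.
- Rejection = 1 − Φ(1.96 − z) + Φ(−1.96 − z).

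| Centre medians | σ | pooled median | θ | z | rejection |
|---|---|---|---|---|---|
| 20–30 min | 0.44 | 24.8 → 24.1 | 0.517 | 0.58 | 8.9% |
| 22–42 min | 0.44 | 31.3 → 30.0 | 0.525 | 0.86 | 13.8% |
| 20–40 min | 0.38 | 29.3 → 28.0 | 0.529 | 1.01 | 17.4% |

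Simulation agrees for the first two rows (about 8% and 13%). With a quarter lost instead of half, rejection is 6.2% for 20–30 min and 6.9% for 22–42 min. If the reporting fraction instead varies by centre and phase between 0.33 and 1.0, the pooled test rejects in 6%, 8%, 10% and 12% at intraclass correlations of 0.05, 0.10, 0.20 and 0.30.

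**5. What each analysis repairs.** Under the mix shifts, a centre-stratified rank test (van Elteren) returns to about 4–5%. Under drift it does not help: at intraclass correlation 0.05 and between-phase correlation 0.5, both tests reject in 14%. A paired t test on the seven centre-level changes stays at 4–5%.

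**The case against.** A reader might infer that pooling heterogeneous centres by itself makes the type I error differ from 5%, or that the primary p-value is wrong. The documents do not support that. Step 2 shows that the level holds when centre effects and expected mix are stable. Inflation needs drift or a mix shift, and the article quantifies neither.

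The heterogeneity it describes concerns infrastructure, catchment, case load and referral pattern, not door-to-needle time. Drip-and-ship patients are excluded anyway. Unequal volumes, or a one-third loss that is stable across phases, do not move the mix.

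There are partial safeguards: the same centres in both phases, equal observation windows, consecutive enrolment and a monitored screening log. The Discussion also says that centres with medians of 30 min or below were targeted, so the 20–30 min row is closer to the stated selection than the two wider ones, and halved enrolment in two centres is a marked shift.

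All of this stands, and it limits the size of the problem. It does not remove it. The log documents recruitment effort but does not hold each centre's share constant, and nothing in the plan guards against drift within centres.

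**Conclusion.** The concern holds in a conditional form: the stated 5% is not guaranteed. It is about 5% or lower with stable centres and stable mix. It is about 6–13% if centre changes vary with an SD of 5–10% for unrelated reasons. It is about 8–9% under the mix shift with centre medians of 20–30 min, and about 13–17% with the wider spreads. The centre medians, intraclass correlation, drift and within-centre spread are all assumptions, because the article gives none of them. The finding that does not depend on them is that a trial which stresses differences between its centres, and intervenes on centres, has a primary test that makes no use of the within-centre comparison.

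**What to change.** 1. Make the primary test centre-stratified (van Elteren) or centre-adjusted. This stays within the rank-based plan, removes confounding by centre mix and needs no new data. Under the assumed spreads it raises power for a 4-min fall from about 83% to 87% in one simulation and from 84% to 90% in another.
2. Report the seven centre-specific pre-to-post changes with an interval from a centre-level paired analysis, or from a model with a random centre-by-phase effect and small-sample degrees of freedom (about 6). Stratification alone leaves drift uncorrected.
3. Keep medians and interquartile ranges as the descriptive summary, and treat door-to-angio and door-to-groin in the same way.

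The cost is analysis wording and a little more work. The centre-level interval may be wider and its power lower: about 58–70% for a 4-min fall and 80–89% for 5 min in simulation. For that reason, replacing the primary test outright with a log-scale mixed model is more debatable than stratifying it; that would also move the effect measure away from the median. None of these analyses removes a secular trend shared by all seven centres, and the report should say so.

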## Discussion

The STREAM trial will evaluate the effect of a five-step intervention for acute stroke therapy on process times, staff satisfaction and perceived patient safety. The intervention aims at optimizing and standardizing stroke treatment by applying aspects of crew resource management (CRM) and simulation training adapted to acute stroke care. It may provide evidence of efficacy for this composite intervention that could pave the way for the implementation of structured team trainings for acute stroke care, as they are already practiced in other medical disciplines.

In high-reliability environments where decisions are time-critical, structured algorithms based on the principles of crew-resource management help to improve patient safety. Once developed, these SOPs have to be introduced to the entire staff. We hypothesize that simulation training will facilitate the transfer of the new algorithms by allowing experiential learning and self-reflection. To evaluate the safety of our intervention, which aims at accelarating IVT, we will capture intra- and extracranial haemorrhagic complications and will compare the frequency between the pre- and post-interventional phases.

Structured team training based on crew resource management (CRM) has been successfully implemented into emergency medicine, intensive care and surgery. In these contexts, training has led to a significant fall in the mortality rate (up to 18%) (20, 21). To our knowledge, there have been only a few reports on the effect of simulation training on process times in acute stroke care. Existing studies rely on one-time interventions at a simulation facility (22), trained hospitals with little prior experience (23) and/or used retrospective case analyses as a comparator (23, 24). We have previously applied the stroke team approach to the sponsor's stroke admissions team (16) and consequently to our regional stroke network (17), which at the time consisted of seven stroke units. In that study, we found that the intervention (algorithm design, introducing CRM, and simulation training) was effective in reducing the network wide door-to-needle time from a median of 43 min (IQR 30–60 min) to 31 min (IQR 24–42 min) (16) and door-to-groin-time from 59 min (IQR 35–102 min) to 43 min (IQR 28–81 min) (25). However, these studies were limited to a regional network consisting of heterogeneous stroke units of different sizes with and without the capacity for EVT. The multicentric study in the stroke network relied on data entry by the local investigators without central source data verification. By testing the stroke team concept in seven high volume academic tertiary care stroke centers with the 24/7 capacity for thrombectomy in a multicentric pre-test-post-test study, we aim to control some of these limitations and measure the effectiveness of the intervention more reliably. A cluster randomization by center would have been desirable, but the heterogeneity in between centers (e.g., hospital infrastructure, rural vs. urban catchment area, case load, and percentage of drip-and-ship patients) does not permit this. Therefore, we opted for a prospective pre-test-post-test design with central source data monitoring.

Another question is the scalability of our composite intervention. In our regional stroke network, stroke team training could be introduced on a regular basis following the above-named effectiveness study (16). So far, trainings are carried out as part of the cooperation between stroke team trainers from the university hospital with the senior staff of local stroke units. Obstacles to a decentralized implementation of an independent regular training at each site include time and access to a qualification programme for stroke team trainers and to stroke specific teaching materials such as simulation equipment, slide-kits and scripted scenarios. If the STREAM trial demonstrates effectiveness of the intervention, it may further promote stroke team simulation as a versatile tool for the education of inter-professional teams. Since all hospitals participating in this trial are part of and often coordinate regional stroke networks, the intervention could be secondarily propagated to these stroke networks. From the feedback of the participating centers, we hope to get an insight into the possible difficulties faced in the implementation processes.

We acknowledge that there are a few limitations that we could not circumvent when designing this trial: randomization is not possible due to the limited number of centers. Since we targeted high volume centers with a median door-to-needle time of 30 min and below, it will be challenging to show an improvement in the primary endpoint. The success of the intervention will crucially depend on the cooperation of all involved medical disciplines and professionals—a factor that is not easy to foresee in the planning phase of a trial. It will probably not be possible to train all staff members involved in acute stroke therapy during the three *in situ* simulations at each center, so we will have to rely on a snowball effect. Notably, including stroke patients who are able to provide written informed consent or stroke patients with a legal representative implies a selection bias. Finally, it will not be possible to discern the impact of the different levels of our intervention.

Nevertheless, we think that the results of this pragmatic and rigorously controlled trial of workflow-improvement and *in situ* simulation could have an impact on the standards of acute stroke care and the training of junior staff in this field.

